### Hearing outcome

- For each patient the mean difference of the four frequencies (500,1000,2000,4000 Hz) between pre- and postoperative audiograms will be calculated to yield the air-bone gap. Hearing outcomes will be compared between the treatment arms using a mixed model for repeated measures (MMRM) with fixed effects for treatment arm and timepoint (6-18 weeks and 12 months) and their two-way interaction and a random effect for subject. Analyses will be adjusted for the hearing outcome at baseline. Primary inference for hearing outcomes will be based on the estimated mean difference at 12 months. If assumptions of normality of residuals is not met, transformations of the outcome will be considered or alternatively non-parametric tests Mann-Whitney U test will be used to compare the audiological data between the two groups (A,B) separately at 6-18 weeks and 12 months. Hearing results will be visualized using the Amsterdam Hearing Evaluation Plot (AHEP) (28). To illustrate the outcomes of the speech audiograms, a scatterplot will be made according to Stanford medicine. <https://hearingoutcomes.stanford.edu/>

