**Main study parameters/endpoints:** Rates of recurrent or residual cholesteatoma are evaluated by diffusion-weighted magnetic resonance imaging (DW-MRI) and micro-otoscopy after approximately one, three and five years. If diffusion restriction is seen on DW-MRI and/or retraction of the tympanic membrane is seen during micro-otoscopy, suspicion for recurrent or residual disease will be recorded. To confirm the diagnosis and to determine whether the cholesteatoma is either recurrent or residual, we will analyse the tympanic membrane description at the beginning of the revision surgery. All other surgical outcome measures are recorded in the surgical report. Pure tone audiograms, including air and bone conduction, and speech recognition scores are evaluated pre- and postoperatively for each patient. The EQ-5D-5L, HUI-3, iMCQ and iPCQ questionnaires will be filled in once pre- and a two times postoperatively by every patient. The OQUA will be filled in once preoperatively and three times postoperatively. The direct health-care costs will be recorded for the sponsor centre and extrapolated for the whole trial.

**Nature and extent of the burden and risks associated with participation, benefit and group relatedness:** The burden patients will experience by participating in this study will be filling in the questionnaire multiple times. The surgery, along with the imaging procedures (CT and DW-MRI), audiometry and follow-up appointments, is part of standard care and takes place irrespective of participation in this study.

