#### 4.4 Sample size calculation

To detect a clinically relevant outcome of the primary objective (residual or recurrent disease) a sample size of at least 160 participants is needed. To calculate the sample size we used applicable and recent retrospective results of the UMC Utrecht (from January 2015 to March 2020) and reported recurrence rates from a systematic review of the literature, as this represents the most methodologically comparable and robust dataset currently available. We used our results to calculate the sample size needed with a power of 0.80. Relevant clinical difference was set at 20%. The calculation is based on a two independent proportions power analysis using a Z test with pooled variance with a alpha of 0.05 and a power of 0.80. Sample size calculations were performed with PASS 2008 and resulted in 80 patients per arm. To compensate for potential dropouts, a 10% margin is implemented, **resulting in 178 patients in total.**

| Two Independent Proportions (Null Case) Power Analysis                    |                               |                               |                                     |                                   |                     |                     |                 |                 |        |
|---------------------------------------------------------------------------|-------------------------------|-------------------------------|-------------------------------------|-----------------------------------|---------------------|---------------------|-----------------|-----------------|--------|
| Numeric Results of Tests Based on the Difference: P1 - P2                 |                               |                               |                                     |                                   |                     |                     |                 |                 |        |
| H0: P1-P2=0. H1: P1-P2=D1<>0. Test Statistic: Z test with pooled variance |                               |                               |                                     |                                   |                     |                     |                 |                 |        |
|                                                                           | Sample
Size
Grp 1
N1 | Sample
Size
Grp 2
N2 | Prop H1
Grp 1 or
Trtmnt
P1 | Prop
Grp 2 or
Control
P2 | Diff
if H0
D0 | Diff
if H1
D1 | Target
Alpha | Actual
Alpha | Beta   |

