#### 6.1.2 Secondary study parameters/endpoints

- **Baseline characteristics:**
  - Patient demographics (age (as collected by birthyear), gender), date of first presentation at the outpatient clinic, date of surgery, operated side (right/left), applied antibiotic treatment within in 2 weeks prior to surgery.
  - Co-morbidities and lifestyle factors: smoking, obesity, asthma, diabetes, COPD, allergies, rhinosinusitis.
  - Amount and type of all previous ear surgeries which are not mentioned in the exclusion criteria.
- **Hearing outcome:**
  - As measured by audiometric testing (pure-tone average thresholds (PTA) as calculated over 0.5, 1, 2 and 4 kHz for the air-conduction (AC) and bone-conduction (BC) and speech audiometry. This will be measured before the surgery, and at 6-18 weeks and around 1 year after surgery. The pre-operative audiogram should not have been measured more than 6 months prior to surgery.

- **Surgical characteristics:**

- A short 'standard' surgical report/template written by the participating otologists per center will be collected and used in the scientific publication to demonstrate any potential differences in surgical technique. This **does not** include patient information.
- STAMCO-classification: Localization and extension of the cholesteatoma, presence of preoperative complication status and the ossicular chain status before/at the time of removal of the cholesteatoma will be recorded. Any differences in outcomes in STAMCO classifications between the two randomized groups will be evaluated and described.

**Figure 2:** Localization, disease extension and complications as described by the STAMCO classification (18, ten Tije et al.)

[figure not shown]

- Material used for obliteration (Bonalive®, bonedust, hydroxyapatite, cartilage, muscle) as registered in the surgical report.

- Ossicular chain reconstruction (OCR); performed (yes/no), if yes, the used material and type of reconstruction (PORP, TORP, use of incus interposition, type 3 tympanoplasty) will also be reported.
- Surgical personnel: It is registered if an ENT-doctor in training (resident) or fellow has operated along with the specialist.
- Surgical time: Surgery time is recorded in minutes for each surgery and described.
- Revision surgery during follow-up: the information and observations as gathered by the surgical report will be collected from all revision surgeries performed during the follow-up of this study.
- **Complications**

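### Section 8.2 labels a pre- to postoperative threshold change as the air-bone gap, so the hearing measure to be modelled is not identified

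*Protocol*

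**What the plan says.** Protocol Section 8.2, Hearing outcome, states the derivation: "the mean difference of the four frequencies (500,1000,2000,4000 Hz) between pre- and postoperative audiograms will be calculated to yield the air-bone gap". The sentence names neither conduction type.

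The same paragraph then sets the model: "Hearing outcomes will be compared between the treatment arms using a mixed model for repeated measures (MMRM"), with effects for arm, visit (6-18 weeks and 12 months) and their interaction. It adds "Analyses will be adjusted for the hearing outcome at baseline" and "Primary inference for hearing outcomes will be based on the estimated mean difference at 12 months". The dependent variable is called only hearing outcomes.

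Section 6.1.2 describes the hearing endpoint differently, as "pure-tone average thresholds (PTA) as calculated over 0.5, 1, 2 and 4 kHz for the air-conduction (AC) and bone-conduction (BC"), together with speech audiometry. On timing it says "This will be measured before the surgery, and at 6-18 weeks and around 1 year after surgery". The Summary confirms what is collected: "Pure tone audiograms, including air and bone conduction, and speech recognition scores are evaluated pre- and postoperatively for each patient".

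The term air-bone gap appears only in Section 8.2, so no other section supplies or corrects its definition.

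**The concern.** The stated calculation cannot produce the quantity it is said to produce. Subtracting one audiogram from another gives a change over time. An air-bone gap needs AC and BC from the same audiogram. An analyst who follows the sentence literally would compute a threshold change and report it as an air-bone gap.

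The distinction matters in this trial. Section 1 links the hearing risk of epitympanic obliteration to removal of part of the malleus and incus, which is a conductive mechanism. Section 6.1.2 separately lists inner-ear damage with perceptive hearing loss as a surgical complication. AC change contains both effects, BC change reflects the inner-ear part, and the gap is their difference. A mislabelled measure blurs these.

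Hearing is also the first secondary objective listed in Section 2. While the modelled measure is unnamed, the choice between AC, BC and gap stays open until the data are in hand, and Section 6.2 says that only participants are blinded.

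**Working it through.** **The plan's own figure.** Hearing has no stated effect size, standard deviation or power. The only computed design figure is the primary sample size in Section 4.4, based on a "two independent proportions power analysis using a Z test with pooled variance with a alpha of 0.05 and a power of 0.80". Exact enumeration of that test with 80 per arm and proportions 0.20 and 0.40 gives power 0.8009 and, at a common proportion of 0.40, alpha 0.0472. Both match the table, and 160 / 0.90 = 178. None of this depends on the hearing definition.

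**Step 1: definitions.** All averages are over 0.5, 1, 2 and 4 kHz.
- Gap at one visit: ABG = AC - BC, same audiogram.
- Change in a measure: postoperative minus preoperative.
- Literal reading of Section 8.2: AC change or BC change. Which one is not stated.

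**Step 2: how they relate.**

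ABG change = (AC post - BC post) - (AC pre - BC pre) = AC change - BC change.

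So AC change equals ABG change only when BC is unchanged, and neither AC change nor BC change is an ABG.

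**Step 3: illustration.** The protocol gives no audiometric values. The thresholds below (dB) are assumptions chosen to span the possibilities.

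| Case | AC pre to post | BC pre to post | AC change | BC change | ABG pre to post | ABG change |
|---|---|---|---|---|---|---|
| 1 | 50 to 40 | 20 to 20 | -10 | 0 | 30 to 20 | -10 |
| 2 | 50 to 45 | 15 to 20 | -5 | +5 | 35 to 25 | -10 |
| 3 | 50 to 50 | 20 to 30 | 0 | +10 | 30 to 20 | -10 |
| 4 | 50 to 40 | 20 to 10 | -10 | -10 | 30 to 30 | 0 |
| 5 | 50 to 60 | 20 to 30 | +10 | +10 | 30 to 30 | 0 |

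In case 1 AC change and ABG change agree. In case 2 the literal formula gives -5 on AC but +5 on BC, so its result depends on a choice the text does not make. In case 3 the gap closes by 10 dB with no gain in AC, only because BC worsened. In case 5 AC worsens by 10 dB and the gap does not move.

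**Step 4: the comparison between arms.** Write D for the mean change in group B minus that in group A. Averaging Step 2 within arms gives D(ABG) = D(AC) - D(BC). The two contrasts differ by D(BC) alone. The protocol gives no figure for D(BC). If it were 0, 5 or 10 dB, the contrasts would differ by 0, 5 or 10 dB. These are assumed values, not estimates.

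**Step 5: the baseline covariate.** Suppose the postoperative value is modelled as a + b × baseline + treatment effect. Subtracting baseline from both sides gives change = a + (b - 1) × baseline + the same treatment effect. With a common baseline slope, modelling the change or the postoperative value gives the same arm difference. The difficulty is only that an unnamed measure has an unnamed baseline.

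**The case against.** **This is compressed wording.** The sponsor may have meant the change in air-bone gap from before to after surgery, and using that term already implies that AC and BC are both needed. That reading is plausible, and both are collected. But the step that subtracts BC from AC is absent, and no other section restores it.

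**The model does not use the faulty formula.** This stands. The model sentence refers to hearing outcomes, which Section 6.1.2 describes as AC and BC averages plus speech audiometry. A reader might infer that the trial will certainly analyse the wrong quantity. The protocol does not show that; it shows that the quantity is undetermined.

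**Baseline adjustment conflicts with a change score.** A reader might infer this because a change has no baseline value of its own. It is not a conflict: the underlying measure has a baseline, and adjusting a change for it is ordinary analysis of covariance (Step 5).

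**The air-bone gap is the better outcome.** A reader might also infer this. The protocol does not say so, and case 3 shows why the gap alone can mislead. The choice of measure is the sponsor's.

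**Derivations belong in the statistical analysis plan.** Often they do, and a plan not seen here may be exact. But the protocol does not leave the matter open. It fixes a derivation that does not give what it names, and a correct plan would have to depart from it.

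**Conclusion.** The derivation in Section 8.2 is wrong as written. It describes a threshold change, calls it an air-bone gap, and does not say which thresholds enter. As a result, neither the model outcome nor its baseline covariate is identified, and the section does not match Section 6.1.2.

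For an individual patient, AC change and ABG change differ by the BC change. For the treatment comparison, they differ by the between-arm difference in BC change. No shift in that comparison has been shown, because the protocol offers nothing from which to estimate it.

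The conclusion rests on the usual meaning of an air-bone gap; the decibel values only illustrate it. This is a secondary endpoint, and the primary endpoint, sample size and data collection are unaffected. Moderate severity is appropriate, and a reader who infers that the trial's main conclusion is at risk would be going too far.

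**What to change.** Replace the derivation sentence in Section 8.2 with text that does the following:

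1. Defines the air-bone gap at each visit as the mean AC minus the mean BC threshold over 0.5, 1, 2 and 4 kHz of the same audiogram.
2. States which measure (air-bone gap, AC average or BC average) is the mixed-model outcome at 6-18 weeks and 12 months, and that the model adjusts for the same measure preoperatively. The rank-test fallback should use the measure so named.
3. Reports AC and BC averages alongside, so that closure of the gap through bone-conduction loss is visible.

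Then align the hearing endpoint in Section 6.1.2 with this wording, naming the air-bone gap there if it is to be analysed.

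The cost is a few lines of text. Every threshold needed is already collected before and after surgery, and the sample size does not change. The correction should be in place before any hearing data are analysed.

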## **8. STATISTICAL ANALYSIS**

Data will be collected in Castor EDC and exported for Statistical analysis in IBM SPSS Data will be collected in Castor EDC and exported for Statistical analysis in IBM SPSS Statistics 29.0 (SPSS Inc., Chicago, IL, USA). Data will be presented according to the Consolidated Standards of Reporting Trials (CONSORT) Statement, an international guideline on adequate reporting of RCTs. To assess whether continuous variables are normally distributed, histograms and the Kolmogorov-Smirnoff test will be computed. Continuous data will be expressed as mean  $\pm$  standard deviation (SD) when normally distributed, and as median  $\pm$  interquartile range (IQR) when skewed. Number of cases and percentages will be presented for categorical variables. A p-value of less than 0.05 will be regarded as statistically significant for all calculations.

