### PROM (OQUA)

- The OQUA is a validated otological questionnaire and includes 34 questions, covering eight major types of ear complaints (earache, pressure in the ear, hearing loss, tinnitus, otorrhoea, itch, dizziness, and loss of taste). It measures the frequency and severity of these ear complaints and the impact on quality of life. The frequency of the ear complaints is expressed on a scale from 1-5, whereas the impact on quality of life is answered on a scale from 0-100. OQUA will be compared between treatment arms using a mixed model for repeated measures (MMRM) with fixed effects for treatment arm and timepoint (12 months, 36 months) and their two-way interaction. Analyses will be adjusted for OQUA at baseline. Primary inference will be based on the estimated mean difference at 36 months.

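### The hearing model names only a random subject effect, so with ordinary residuals the 12-month standard error pools the variances of both visits; an unstructured covariance removes that dependence

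*Protocol*

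**What the plan says.** Section 6.1.2 sets the audiometry schedule: "This will be measured before the surgery, and at 6-18 weeks and around 1 year after surgery". Table 1 gives the later visit a window of one month either side of 12 months. There are therefore two post-operative hearing measurements per patient.

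Section 8.2, Hearing outcome, labels the analysis an MMRM and specifies "fixed effects for treatment arm and timepoint (6-18 weeks and 12 months) and their two-way interaction and a random effect for subject". It adds "Analyses will be adjusted for the hearing outcome at baseline" and names the target: "Primary inference for hearing outcomes will be based on the estimated mean difference at 12 months". The only departure from assumptions that it provides for is non-normality: "If assumptions of normality of residuals is not met, transformations of the outcome will be considered", with a rank test as the alternative. It mentions no residual covariance structure, no separate variance per visit and no robust standard error.

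Section 8 sets the significance level: "A p-value of less than 0.05 will be regarded as statistically significant for all calculations". The protocol gives no standard deviation, effect size or power for hearing.

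**The concern.** A random subject effect with independent residuals of one common variance gives every visit the same total variance. The model then estimates a single variance from both visits and uses it for the 12-month contrast, although only the 12-month variance determines how precise that contrast is.

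The two visits are not alike. The first falls anywhere in a 12-week-wide window soon after surgery; the second is held to within a month of one year. Equal variances are possible, but nothing in the protocol supports them, and the fallback for non-normal residuals would not react if they differed.

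At stake are the confidence interval and p-value for the 12-month hearing difference. Section 1 notes that epitympanic obliteration requires removal of part of the ossicular chain, with a risk to hearing. An interval that is too wide could obscure such a harm; one that is too narrow could suggest a difference that is not there.

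**Working it through.** **Inputs.** Two visits, 6-18 weeks and 12 months (Sections 6.1.2 and 8.2). Level 0.05 (Section 8), taken as two-sided in line with the two-sided alternative in the Section 4.4 table. 80 patients per arm (Section 4.4). Hearing SDs are not given, so the ratio k = early SD / 12-month SD is an assumption.

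**The plan's own figure.** There is none for hearing. The primary-outcome size does reproduce: exact enumeration of the pooled Z test at 80 per arm, 0.20 against 0.40, gives power 0.8009 and alpha 0.0472, as tabulated, and 160 / 0.90 = 177.8, rounded up to 178. The 80 per arm is used below only to size the simulation; the standard-error ratio does not depend on it.

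**Formula.** Let s1 and s2 be the within-arm SDs at the early and 12-month visits, after baseline adjustment, with n per arm and complete data.

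- True SE of the 12-month difference: √(2·s2² / n).
- Under a random intercept with a common residual variance, the fitted variance at either visit is the average (s1² + s2²)/2, so the model SE is √(2·[(s1² + s2²)/2] / n).
- Ratio of model SE to true SE: R = √((k² + 1)/2).
- Real two-sided alpha: 2·Φ(−1.96·R).

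**Results.** The simulated columns come from 20,000 runs per row, with 80 per arm, within-patient correlation 0.5 and no baseline covariate. They use the closed-form complete-data estimator.

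| k | R by formula | 1.96·R | alpha by formula | alpha simulated, pooled variance | alpha simulated, separate variance per visit |
|---|---|---|---|---|---|
| 1.5 | √(3.25/2) = 1.275 | 2.499 | 0.0125 | 0.015 | 0.051 |
| 1.25 | √(2.5625/2) = 1.132 | 2.219 | 0.0265 | 0.029 | 0.053 |
| 1.0 | 1.000 | 1.960 | 0.050 | 0.051 | 0.050 |
| 0.8 | √(1.64/2) = 0.906 | 1.775 | 0.076 | 0.080 | 0.052 |
| 0.67 | √(1.444/2) = 0.850 | 1.666 | 0.096 | 0.099 | 0.052 |

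A second set of 20,000 runs per ratio, this time with baseline adjustment, gave alpha of 0.013, 0.025 and 0.079 for k = 1.5, 1.25 and 0.8, and 0.051-0.053 when the 12-month variance was estimated on its own. The two sets agree with each other and with the formula. Scenarios with missing visits were not simulated.

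**The point estimate.** With complete data and an arm-by-visit interaction, the 12-month contrast is the difference in 12-month means under either covariance, apart from a small effect through the baseline slope. The choice of covariance changes mainly the SE, the interval and the p-value.

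**The case against.** The strongest reply is that the protocol never says the residuals are independent with one variance. It calls the model an MMRM. A random intercept combined with visit-specific residual variances has three covariance parameters for two visits and, if the within-patient covariance is not negative, gives the same 2×2 matrix as an unstructured model. Residual covariance for a secondary model is also ordinary SAP material, and the SAP is not at hand.

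Part of this stands. A reader might infer that the stated model forces equal variances; the text supports that only under default residuals. But the protocol does more than stay silent: it names a within-patient structure, and the ordinary reading of it is compound symmetry. The MMRM label does not settle the matter either. If it means an unstructured residual matrix, a random intercept on top is redundant and cannot be identified from two visits. The reading that works, separate residual variances by visit, is not written down.

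The reply is also right that no evidence of unequal variances is given. The one design argument, the wide early window, points to a noisier first visit and hence to a conservative 12-month test. A reader might infer an inflated false-positive rate; that needs the opposite case, a noisier 12-month visit, for which the protocol offers no reason.

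Two extensions do not hold. The OQUA model is written with "fixed effects for treatment arm and timepoint (12 months, 36 months) and their two-way interaction" and no random subject effect, so its covariance is merely unstated and can be left to the SAP. A baseline-by-visit slope might be preferred for efficiency, but there is no figure behind it, and with randomised arms a common slope does not bias the 12-month contrast in expectation.

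**Conclusion.** The point holds in a limited form. Read in its ordinary sense, the stated hearing model gives a correct 12-month standard error only if the two visit variances are equal, and it does not need that assumption.

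Over assumed SD ratios (early / 12-month) of 1.5 to 0.8 with complete data, the standard error runs from about 27% too large to about 9-10% too small, and alpha from about 0.013 to about 0.076-0.08. At a ratio of 1.0 there is no error. These figures rest on default residuals and on SD ratios that the protocol does not supply, so neither the size nor the direction is known.

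A reader might infer that the 12-month precision is taken from the early visit. It is not: the two visits contribute equally, and half the variance still comes from 12 months.

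The recidivism analysis and the sample size are untouched. This is a low-cost improvement to a secondary analysis.

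**What to change.** In Section 8.2, Hearing outcome, replace the clause naming the random subject effect with: *an unstructured within-patient covariance matrix over the two visits*. The fixed effects, baseline adjustment and 12-month target stay as they are. In SPSS, which Section 8 names, this is fitted in MIXED through the REPEATED statement, without a random intercept.

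The cost is one extra covariance parameter (three instead of two), no extra data, and essentially no loss if the variances are equal: simulated alpha is 0.050 at k = 1.0. The change should be made before hearing data are examined, so that it cannot look data-driven.

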Whether surgeons do or do not obliterate the mastoid cavity after CWU tympanomastoidectomy today, seems to depend mostly on their personal experience, preferences, and scientific beliefs. Within the present ENT community, the usefulness of the obliteration is still widely discussed and is still a topic of current interest in literature, during congresses and within ENT-societies. The superiority of the technique is merely explored retrospectively in the literature with several confounding factors and a high risk of bias (such as difference in but not limited to; patient-related factors, surgical technique; obliteration material; follow-up periods; exclusion/inclusion criteria). Furthermore, current research rarely categorizes outcomes based on cholesteatoma extension and localisation, as for example classified using the STAMCO stages (18).

In addition to recidivism of cholesteatoma, hearing is another important outcome measure. In the literature, most research is conducted on hearing outcomes after CWD or canal wall reconstruction surgery with mastoid and epitympanic obliteration. Numerous studies show that these two similar techniques preserve preoperative hearing outcomes, or even moderately improve it (19–23). However, there is limited literature available on hearing outcomes following CWU with obliteration. The few retrospective studies that have recently been carried out show promising results that this approach also ensures hearing preservation (24–26). When using the obliteration technique in the epitympanum (a part of the middle ear), a part of the ossicular chain (part of the malleus and incus) must be removed, which poses a risk for hearing loss after surgery. It is therefore useful to investigate the relation between CWU tympanomastoidectomy with obliteration and hearing outcomes to either confirm or deny the retrospective evidence that recurrence and residual rates are lower due to the obliteration.

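### If residuals look non-normal, the hearing analysis may switch to a transformed outcome or an unadjusted Mann-Whitney U test, and neither gives the baseline-adjusted mean difference at 12 months named for primary hearing inference

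*Protocol*

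**What the plan says.** Everything at issue stands in one paragraph, Protocol section 8.2, Hearing outcome.

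- The planned analysis is a mixed model for repeated measures over the two postoperative visits (6-18 weeks and 12 months). On covariates: "Analyses will be adjusted for the hearing outcome at baseline".
- The target is explicit: "Primary inference for hearing outcomes will be based on the estimated mean difference at 12 months".
- The exception follows at once. When the residuals fail a normality check, a transformation may be tried. The other option reads: "alternatively non-parametric tests Mann-Whitney U test will be used to compare the audiological data between the two groups (A,B) separately". That test is run once for each postoperative visit.
- The analysed value is not clear. The paragraph opens with a difference over four frequencies "between pre- and postoperative audiograms will be calculated to yield the air-bone gap", so the rank test could be applied to postoperative values or to pre-to-post changes.

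The paragraph does not say what counts as a failed normality check, which of the two alternatives then applies, or whether the mean difference stays primary. Section 8 sets the threshold for all tests: "A p-value of less than 0.05 will be regarded as statistically significant for all calculations".

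**The concern.** The paragraph names a quantity and then permits analyses that cannot produce it.

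- **Transformation.** An effect estimated on, say, a log scale is not a mean difference in dB.
- **Mann-Whitney.** The test takes no covariate, so the required baseline adjustment is lost. Its null hypothesis is that the two distributions are identical, not that the means are equal. It gives no mean difference.

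Hearing is the first secondary objective in section 2, and readers will look for an effect in dB with an interval. As written, that estimate might not appear, and a significant rank test could be read as a difference in mean hearing when it need not be one.

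**Working it through.** **The plan's own figure.** The only sample size calculation (section 4.4) is for recidivism: 20% v 40%, two-sided pooled Z test, alpha 0.05. Exact binomial enumeration at 80 per arm gives power 0.8009, and a rejection rate of 0.0472 when both proportions are 0.40. Both match the protocol's table. With 10% dropout, 160/0.9 = 177.8, hence 178. No power is stated for hearing. The 80 per arm is carried forward.

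**Inputs for hearing.** The protocol gives no SD, correlation or residual shape. Assumed: outcome SD 1 (so shifts are in SD units), baseline to 12-month correlation ρ of 0.3 to 0.7, and exponential-type skew. A baseline-adjusted comparison at 12 months (ANCOVA) stands in for the model contrast.

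**Step 1: error rates and the hypothesis tested.** Outcome = ρ × baseline + residual, with residual SD √(1−ρ²) times a multiplier; 80 per arm, 2,000 trials per row. Monte Carlo standard error at 5% is √(0.05 × 0.95/2000) = 0.5 points. Entries are rejection rates (%).

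| Scenario | ρ | Adjusted mean | Mann-Whitney, postoperative | Mann-Whitney, change |
|---|---|---|---|---|
| No effect, same skewed distribution | 0.5 | 4.5 | 5.0 | 4.9 |
| | 0.7 | 5.6 | 5.3 | 5.2 |
| Equal means, skewed, SD multipliers 1.5 v 0.75 | 0.5 | 5.4 | 22.7 | 23.1 |
| | 0.7 | 5.0 | 9.8 | 33.2 |
| Equal means, only one arm skewed | 0.5 | 5.0 | 7.7 | 8.5 |
| | 0.7 | 5.3 | 5.4 | 10.5 |
| Equal residual medians, different means | 0.5 | 19.0 | 5.0 | 5.9 |
| | 0.7 | 19.1 | 5.6 | 5.8 |

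A further set of runs put Mann-Whitney rejection under equal means and unequal spread at about 7% to 33%, with the adjusted mean test at 4% to 6%. So skew alone does not upset the adjusted mean test at this size, and the rank test answers a different question in both directions.

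**Step 2: power, normal errors.** Choose the shift that gives the adjusted test 80% power:

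δ = (1.960 + 0.842) × √(2/80) × √(1−ρ²) = 0.423, 0.384 and 0.316 SD at ρ = 0.3, 0.5 and 0.7.

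Mann-Whitney on postoperative values ignores baseline (SD 1) and has relative efficiency 0.955 under normality:

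power = Φ(δ√0.955/√(2/80) − 1.960) = 74%, 66% and 50%.

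Simulation at ρ = 0.5 and 0.7 gives 64.6% and 49.0% on postoperative values, and 65.5% and 70.7% on change scores.

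For a fixed shift of 0.35 SD at ρ = 0.7:

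- Adjusted test: 0.35/(0.1581 × 0.714) − 1.960 = 1.14, power 87%.
- Mann-Whitney, postoperative: 0.35 × 0.977/0.1581 − 1.960 = 0.20, power 58%. Simulation gave 59% to 63%.

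**Step 3: power, skewed errors, pure shift.** Here the comparison can reverse. With the Step 2 shifts at ρ = 0.5, the rates are 79% adjusted, 78% postoperative ranks and 79% change-score ranks. At ρ = 0.7 they are 79%, 53.5% and 88.7%. For the 0.35 SD shift at ρ = 0.7 with strong skew (gamma shape 1), the adjusted test with robust errors has 86% and Mann-Whitney on change scores 93%.

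**The case against.** The strongest defence is that this is a pre-named contingency for a secondary outcome. The adjusted model remains the plan, the rank test is reached only if normality fails and transformation is passed over, and rank methods fit the protocol's use of medians for skewed data. All true, and it limits the weight of the point. It does not supply the missing estimate: the paragraph names a mean difference, and neither alternative returns one.

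Four stronger readings are tempting and are not supported.

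- **That the fallback inflates the false-positive rate in this trial.** This needs arms that differ in spread or shape. The Introduction says that with epitympanic obliteration "a part of the ossicular chain (part of the malleus and incus) must be removed, which poses a risk for hearing loss after surgery". That states a risk of hearing loss, not unequal spread. A simulated mixture built on that mechanism gave only 5% to 7%. Moreover, if the distributions differ, a rejection is correct for the test's own null. The fault is the change of question.
- **That power is necessarily lost.** The loss holds for postoperative values. For change scores baseline is already subtracted, and with skewed data the rank test can do as well or better. The text does not settle which is tested.
- **That testing each visit separately wastes the early audiogram for patients missing at 12 months.** The end of section 8.2 provides for multiple imputation, and an imputation model can use the 6-18-week and baseline values.
- **That the trial's main conclusion is at risk.** Recidivism is analysed separately and is untouched.

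A statistical analysis plan might settle the choice between the options. The conflict between the named estimate and both alternatives is, however, fixed in the protocol's own text.

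**Conclusion.** The point holds in limited form. The fallback sentence contradicts the two sentences around it: the transformation abandons the dB scale, and the Mann-Whitney test abandons the mean, the baseline adjustment and the hypothesis. It is also unnecessary, since under the skew assumed here the adjusted mean test held 4% to 6% error at 80 per arm.

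The practical size depends on facts the protocol does not give. With equal means, Mann-Whitney rejects in about 5% of trials if the arms share a distribution, and in about 7% to 33% if they differ in spread as assumed. Power at ρ = 0.7 and a 0.35 SD shift ranges from about 60% (postoperative values) to 93% (change scores, strong skew), against 86% to 87% for the adjusted test. These figures illustrate what could happen and are not predictions. The consequence is moderate and confined to a secondary outcome, but the correction is nearly free and should be made.

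**What to change.** Replace the fallback sentence in section 8.2 with text to this effect: the baseline-adjusted mean difference at 12 months from the repeated-measures model, in dB, is reported as the primary hearing inference whatever the residual shape; robust (sandwich) or patient-level bootstrap standard errors are used from the outset; any transformed or rank-based analysis, preferably baseline-adjusted, is a sensitivity analysis.

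Using robust or bootstrap errors from the start, rather than after a failed check, removes the data-driven switch. It also makes the unclear outcome definition matter less here. If postoperative value y = α + τ × arm + β × baseline + error, then change y − baseline = α + τ × arm + (β − 1) × baseline + error, so the arm difference τ is the same for either. The paragraph should still state which value is analysed.

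The cost is one sentence and a software option, with no new data. With strongly skewed data there is a slight loss of efficiency against a rank test on change scores.
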